## Abstract

**Background:**

In the United Kingdom, the prevalence of diabetes‐related foot ulcer disease (DFUD) is 6.3%, and cardiovascular disease (CVD) is the leading cause of mortality in people with DFUD. This study aims to evaluate the effectiveness of a multifactorial intervention to reduce CVD events and mortality in adults with type 2 diabetes (T2D) and DFUD.

**Methods:**

The MiFoot study is a multi‐centre, pragmatic randomised controlled trial to test intervention effectiveness and cost‐effectiveness compared to usual care that will include an internal feasibility study and a process evaluation. English‐speaking adults (≥18 years; *n* = 392) with T2D and current/previous (within 5 years) DFUD will be recruited from multiple sites across the United Kingdom and randomised 1:1 to intervention (MiFoot multifactorial intervention plus usual care) or control (usual care), with data collected at baseline, 12‐ and 24‐month follow‐up. The MiFoot intervention comprises an individualised assessment with a healthcare practitioner to optimise treatment and assess the suitability of physical activity participation; group‐based disease self management education and physical activity sessions; and a digital‐based programme, consisting of cohort‐relevant topics, physical activity guidance and peer support functionality. The primary outcome will be extended major adverse cardiovascular events (MACE, i.e. myocardial infarction, stroke, cardiovascular death, peripheral arterial bypass, coronary artery bypass, coronary angioplasty or peripheral artery angioplasty) at 24 months.

**DISCUSSION:**

This study will provide evidence on the feasibility and clinical effectiveness, and cost‐effectiveness of a multifactorial intervention to prevent or slow the progression of CVD‐related complications in the extremely high‐risk population with T2D and DFUD.

## INTRODUCTION

1

Diabetes‐related foot ulcer disease (DFUD), defined as an ulcer below the malleoli, is a devastating complication of diabetes and is associated with significantly increased risks of cardiovascular disease (CVD) and premature mortality.^1^ In the United Kingdom, the prevalence of DFUD is 6.3%,^2^ and prevalence and disease burden are substantially higher in people with Type 2 (T2D) than Type 1 (T1D)^3^ diabetes. Five‐year mortality in individuals with DFUD is 40%,^4^ which is worse than many cancers; yet DFUD is consistently perceived as less life‐threatening.^5^ Moreover, the financial burden of DFUD on the NHS is higher than that of breast, prostate and lung cancer combined.^6^

While CVD is the leading cause of death in people with DFUD,^7^ research conducted in people with DFUD typically focuses on ulcer prevention and management.^8^ Although imposed physical inactivity and immobilisation with other long‐term conditions in DFUD drive CVD risks,^9^, ^10^ they do not entirely account for the excess CVD burden seen in this population. Accordingly, research into aggressive CVD risk modification in people with DFUD is of clinical relevance.

There is evidence of improved CVD risk from structured self management education and multiple risk factor control in people with T2D and microalbuminuria.^11^ However, these interventions have not been widely adopted for people with T2D and DFUD. Re‐designing previous high‐quality trials in T2D patients without DFUD specifically for the needs of the DFUD patient groups, for example, by replacing leg load‐bearing physical activity with arm ergometer exercises,^5^ provides an opportunity for clinical benefit in this high‐risk cohort. While there is limited evidence supporting non‐load‐bearing exercises in people with DFUD, there exists some literature on the efficacy of non‐load bearing exercises, either within research or as routine care, and philosophy‐backed behavioural interventions on CVD risks in other chronic diseases.^9^, ^10^, ^12^, ^13^ Therefore, these types of exercises provide opportunities for those with DFUD to gain the cardiovascular benefits of exercise without the risk of further foot problems.^14^ Providing offloading of foot and ankle joints does not have to exclude providing safe, effective, and protective vascular exercises like seated upper body cardiovascular exercise programmes which may be beneficial for people with active foot disease.^15^ Hence, this trial will investigate the clinical and cost effectiveness of a multifactorial complex intervention to prevent or slow the development of CVD‐related complications in people with T2D and DFUD, compared to usual care.

## METHODS

2

### Study design

2.1

The MiFoot study is a multi‐centre, pragmatic randomised controlled trial (RCT) designed to test the clinical and cost‐effectiveness of the MiFoot intervention compared to usual care, with an internal feasibility study and process evaluation. This study was granted a favourable ethical opinion by the North East–York Research Ethics Committee (23/NE/0136), received Health Research Authority approval, and has been prospectively registered on the Clinical Trials Registry (https://www.isrctn.com/ISRCTN13413505). Figure 1 describes participants progression through the study.

**FIGURE 1 dme70028-fig-0001:**
[figure not shown]
Schematic representation of the processes of the study.

### Aims

2.2

Primary aim: Compare the MiFoot intervention with usual care for the prevention of CVD events in people with T2D and current or previous DFUD.

Secondary aims include: (1) Estimate the cost‐effectiveness of the MiFoot programme in a real‐world clinical setting; (2) Evaluate the sustainability of the programme by completing a process evaluation; and (3) Monitor the recruitment and stop‐go criteria with an internal feasibility study.

### Study population

2.3

#### Inclusion and exclusion criteria

2.3.1

The study will include adults diagnosed with T2D and with current or previous (within the past 5 years) DFUD. Participants must understand English, be able and willing to fulfil the study requirements and not currently be taking part in a clinical trial for an investigational medicinal product or any other disease management or lifestyle‐related intervention trial. Patients diagnosed with other forms of diabetes and forms of ulceration not attributable to peripheral neuropathy or peripheral vascular disease will be excluded, as well as patients with serious illnesses or events associated with a life expectancy of <1 year. Patients unable to provide consent, with a planned major surgery, or requiring renal replacement therapy, who are currently pregnant or actively trying to conceive, will be excluded.

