#### Baseline research data extraction

2.4.3

Routine health data, medical history, all current diagnoses and dates, procedures/surgeries and medications, will be extracted from participants' medical records. Routine biomarker results, as listed in Table 1, that are within 6 months, will be extracted or requested through the GP.

**TABLE 1 dme70028-tbl-0001:** Secondary outcomes, measures and time of measurement during the study.

Secondary outcomes	Measures	Visits		
		Baseline visit, Month 0	Remote, 12‐month follow‐up	Remote, 24‐month follow‐up
Health outcomes	Composite renal end points: End‐stage kidney disease (defined as dialysis, transplantation, or a sustained (>3 months) estimated Glomerular Filtration Rate [eGFR] of <15 mL/min/1.73 m^2^) Doubling of the serum creatinine level Or death from renal causes 3‐Point MACE (non‐fatal myocardial infarction, non‐fatal stroke and cardiovascular death) and components of the extended MACE All‐cause mortality Lower limb major amputation Self reported re‐ulceration		X	X
Patient‐reported outcomes	Using Questionnaires: Distress using Problem Area in Diabetes‐20 (PAID‐20) Self‐efficacy using Diabetes Management Self‐Efficacy Scale‐15 (DMSES‐15) Quality of Life using Diabetes Foot Ulcer Disease (Diabetes Foot Scale‐Short Form [DFS‐SF], generic EuroQoL‐5Dimension‐5Levels [EQ‐5D‐5L]) Depression and anxiety using Hospital Anxiety and Depression Scale (HADS) Health resource use, such as primary care visits, emergency department visits, hospitalisations and medication use using Modular Resource‐Use Measure (ModRUM) Medication adherence using the Morisky Medication Adherence Scale (MMAS‐8) Diet using the Short Form Food Frequency Questionnaire Sleep duration/quality and physical activity volume/intensity measured objectively using wrist worn accelerometers	X	X	X
Biomedical markers	Blood pressure (systolic, diastolic and heart rate) (mmHg, BPM) Low‐density lipoprotein‐cholesterol (LDL‐C) (mmol/L) High‐density lipoprotein‐cholesterol (HDL‐C) (mmol/L) Total cholesterol (TC) (mmol/L) Triglycerides (TG) (mmol/L) Glycated haemoglobin (HbA1c) (% and mmol/mol) Estimated Glomerular Filtration Rate (eGFR) (mL/min/1.73 m2) Urine albumin: creatinine ratio (uACR).	X	X	X
Anthropometric	Weight Body mass index (BMI)	X	X	X

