## Outcomes

3

The primary outcome is the incidence of extended Major Adverse Cardiovascular Events (MACE) at 24 months, identified using routine healthcare data. The extended MACE definition for MiFoot is context‐specific and is defined as myocardial infarction, stroke, cardiovascular death, peripheral arterial bypass, coronary artery bypass, coronary angioplasty or peripheral artery angioplasty.^16^ The secondary outcomes are health, patient‐reported, biomedical and anthropometric outcomes, described in Table 1.

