## Sample size calculation

4

Three hundred and ninety‐two participants will be recruited across all sites. This calculation is based on detecting a 20% improvement in the survival rate for extended MACE (a much smaller reduction than a similar intervention in another high risk T2D population^17^) at 24 months from 65.6% (34.4% experience an event) to 78.7% (21.3% experience an event). The 65.6% rate in the control arm at 24 months was extrapolated from two of our previous studies in this population.^11^, ^18^ Assuming 80% power and 5% alpha, a sample size of 372 participants is required. Allowing for a 5% drop out (low because primary outcome will be collected by data linkage) similar to previous work,^14^ the number of participants required increases to 392. The sample size calculation may be proactively refined if any further relevant data emerge in the literature during the study.

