## Statistical analysis

7

A full statistical plan will be finalised prior to database lock before any unblinded data has been seen by the statistician. The primary analysis will compare the primary outcome (extended MACE at 24 months) between treatment groups using a Cox proportional hazards regression model, assuming assumptions are met. The model will be fitted with time to extended MACE as the outcome and treatment group as the main explanatory variable. The stratification factors (site, age, sex) will be adjusted for, and participants lost to follow‐up will be censored at the last date at which they were known to be event‐free. If any baseline imbalances become evident, these will be investigated using secondary exploratory analyses.

For the event outcomes (renal end points, extended MACE components and all‐cause mortality, amputation), the analysis approach will be a Cox proportional hazards model adjusted for the stratification factors in line with the primary analysis. The questionnaire summary measures, biomedical markers and anthropometric measures will be compared between treatment groups using linear mixed regression models adjusted for time (baseline, 12 and 24 months) and the stratification factors. Missing data for non‐event outcomes will be imputed using multiple imputation where data can be assumed to be missing at random. A sensitivity analysis will be carried out removing any variables with >10% missing data.

Summary measures (number of events or mean change from baseline) by treatment group, effect size, 95% confidence interval and two‐sided *p*‐value will be presented for each of the primary and secondary analyses. Statistical significance will be assessed at the 5% level.

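### An angioplasty already planned at enrolment is not clearly excluded and, as written, can count as a first extended MACE that neither arm can prevent

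*Protocol article*

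**What the plan says.** Four parts of the protocol article bear on this.

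- **Inclusion and exclusion criteria (2.3.1).** People with a present ulcer, or one in the preceding five years, can join. Ulcers "not attributable to peripheral neuropathy or peripheral vascular disease will be excluded", so an ischaemic ulcer qualifies. The only exclusion that touches planned procedures is in the sentence beginning "Patients unable to provide consent, with a planned major surgery, or requiring renal replacement therapy". The article does not define major surgery.
- **Outcomes (3).** Extended MACE includes peripheral bypass and "coronary artery bypass, coronary angioplasty or peripheral artery angioplasty". Events come from routine healthcare data. The definition neither limits these procedures to those decided after randomisation nor says that planned ones count.
- **Baseline research data extraction (2.4.3).** History, diagnoses, procedures and medications "will be extracted from participants' medical records". The article names no item for a procedure that is listed but not yet done.
- **Blinding (2.4.8).** The study team is not blinded, and the article says that no outcome assessors are involved. It describes no step at which a pre-planned procedure would be set aside.

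The primary analysis is a Cox model of time to extended MACE over 24 months.

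**The concern.** The primary aim is prevention of cardiovascular events. Take a participant with an open ischaemic ulcer who is already listed for peripheral angioplasty at enrolment. Nothing in the article clearly makes this person ineligible. Once the procedure is done, routine records show a component of the primary outcome. The decision came before allocation, so the programme cannot change it.

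Two things follow. The event adds equally to both arms and pulls the hazard ratio towards 1. It also ends that participant's time at risk in the primary analysis, so a later myocardial infarction or stroke does not enter the main comparison. The sample size is set at 80% power with no margin, so any dilution takes the trial below its target.

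**Working it through.** **Inputs from the article.** Sample size calculation: control event rate 34.4%, intervention 21.3%, and "Assuming 80% power and 5% alpha, a sample size of 372 participants is required", rising to 392 for 5% dropout. Statistical analysis: "Statistical significance will be assessed at the 5% level", with two-sided p-values. Allocation is 1:1, so 186 evaluable per arm.

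**Input not in the article.** The share f of participants with an angioplasty already planned at enrolment. I assume 1%, 2% and 5%, with 10% as an upper illustration only.

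**Step 1: reproduce the plan's figure.**
- HR = ln(0.787)/ln(0.656) = 0.568.
- Freedman events = (1.960 + 0.842)² × [(1 + 0.568)/(1 − 0.568)]² = 7.849 × 13.19 = 103.5.
- Mean event probability = (0.344 + 0.213)/2 = 0.2785.
- N = 103.5/0.2785 = 371.6, so 372. With dropout, 372/0.95 = 391.6, so 392. Both match.
- Power at 372: events = 372 × 0.2785 = 103.6; z = √103.6 × (1 − 0.568)/(1 + 0.568) − 1.960 = 0.843; power 80.0%.

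**Step 2: planned procedures inside the 34.4%.** Everyone else has HR 0.568.
- Control risk among the others: q = (0.344 − f)/(1 − f).
- Their intervention risk: t = 1 − (1 − q)^0.568.
- Intervention-arm risk: P2 = f + (1 − f)t. Observed HR = ln(1 − P2)/ln(0.656). Events = 186 × (0.344 + P2).
- Example, f = 5%: q = 0.294/0.95 = 0.3095; t = 0.1897; P2 = 0.2302; HR = 0.621; events 106.8; z = 0.459; power 68%.

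**Step 3: planned procedures on top of the 34.4%.**
- P1 = f + (1 − f)(0.344) and P2 = f + (1 − f)(0.213).
- Example, f = 5%: 0.3768 and 0.2523; HR = 0.615; events 117.0; power 73%.

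**Step 4: planned procedures not counted.** Affected participants stay at risk at the same rates as the others, so HR returns to 0.568. In the inside case, events = 186 × (q + t). In the on-top case the rates return to 34.4% and 21.3%, and power to 80%.

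| Assumed share f | HR, inside | Power, inside | Power, on top | Power, inside, not counted |
|---|---|---|---|---|
| 0 | 0.57 | 80% | 80% | 80% |
| 1% | 0.58 | 78% | 79% | 79% |
| 2% | 0.59 | 75% | 77% | 78% |
| 5% | 0.62 | 68% | 73% | 76% |
| 10% | 0.68 | 53% | 66% | 70% |

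**Cross-check.** Schoenfeld's formula, with the log HR weighted by the share of preventable events, starts at 82.1%. At 1%, 2%, 5% and 10% it gives 79.5%, 76.7%, 67.5% and 50.2% inside, and 80.3%, 78.5%, 73.0% and 63.6% on top. The pattern is the same.

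**Plausibility.** In the inside case, f = 5% makes 0.05/0.344 = 15% of control events pre-planned angioplasties; f = 10% makes it 29%. By contrast, 1% to 2% is about two to four people per arm of 186.

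**The case against.** The strongest reply is that this argues from silence in a condensed article. The outcome definition is a short list of components, and the meaning of major surgery and the event rules may be set out in a full protocol or endpoint document that is not shown. This limits certainty. It does not remove the point, because the article states both the eligibility rule and the outcome rule, and taken together they leave the case open.

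Other replies carry weight:

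- **Size.** Nothing in the article supports 5% or 10%. Recruitment also runs through volunteer databases, community networks and social media, and people with only a past ulcer are eligible. The share could be small.
- **Design effect.** The control rate "was extrapolated from two of our previous studies in this population". If those studies counted planned procedures, some dilution may already be in the assumed effect. Applying HR 0.568 only to the other participants is a modelling choice.
- **Later events.** Three-point MACE and the components of extended MACE are secondary outcomes, with the components given Cox models of their own. A later infarction or stroke is lost to the primary analysis, not to the trial.
- **Judgement.** Deciding after randomisation whether a procedure was pre-planned would bring in a judgement that the records-based design avoids, made by an unblinded team. This is why the fix must rest on a record made before allocation.

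A reader might also infer more than the text supports: that all four revascularisation components are affected, or that the plan actively counts planned procedures. A listed bypass would ordinarily be excluded as major surgery, and the article never says that planned procedures count.

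**Conclusion.** The point holds for planned angioplasty, coronary or peripheral. The exclusion does not clearly cover it, and the outcome definition does not set it aside, so as written it can be a participant's first primary event.

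The consequence is attenuation and lost power. A reader might infer a biased comparison or an inflated false-positive rate. Neither follows, because the procedures are fixed before allocation and randomisation is expected to balance them.

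The size cannot be established from the article. At an assumed 1% to 2%, the loss is about 1 to 5 percentage points of power. At 5% it is about 7 points (on top of the 34.4%) or 12 points (inside it). These figures assume no treatment effect on the planned procedures, HR 0.568 for everyone else and 372 evaluable participants. This is a cheap improvement worth making, not a fault in the sample size arithmetic, which reproduces.

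**What to change.** 1. At baseline extraction, before allocation, record whether a revascularisation is already planned (yes/no), its type and its vessel territory.
2. State in the primary outcome definition that a procedure so recorded is not an extended MACE, and that the participant stays at risk for later events.
3. Add a sensitivity analysis that counts all procedures, so that the effect of the rule can be seen.
4. Reconcile the exclusion with the outcome definition by stating whether planned angioplasty falls under planned major surgery. That is for the sponsor to decide. If the answer is yes, the field still documents that the exclusion was applied.

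The cost is one extra field, one sentence and a slightly lower event count. Where the planned procedures are part of the 34.4%, not counting them raises power from 75% to 78% at a 2% share and from 68% to 76% at 5%. Because the record is made before allocation, knowledge of the arm cannot influence it. Even if few participants are affected, the field lets the sponsor show that.

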#### Participant identification

2.3.2

Potential participants will be identified via primary and secondary care sites supported by Regional Research Delivery Networks, existing participants on volunteer databases, community organisations and networks, and other avenues including social media. We will leverage equality, diversity and inclusion (EDI) guidelines while promoting, identifying and inviting participants to the study, and will collect EDI‐relevant data (e.g. sociodemographic data).

### Trial procedures

2.4

#### Informed consent

2.4.1

Following eligibility confirmation, participants will be given the opportunity to ask any questions relating to their study involvement and will give informed consent to a healthcare professional (HCP).

#### Baseline measure data collection

2.4.2

Data collected will include participants' age, sex, ethnicity, height, weight, resting heart rate, blood pressure and DFUD severity score based on ulcer Site–Ischemia–Neuropathy–Bacterial‐infection–Area–and Depth (SINBAD), if the participant has an active foot ulcer.

#### Baseline research data extraction

2.4.3

Routine health data, medical history, all current diagnoses and dates, procedures/surgeries and medications, will be extracted from participants' medical records. Routine biomarker results, as listed in Table 1, that are within 6 months, will be extracted or requested through the GP.

**TABLE 1 dme70028-tbl-0001:** Secondary outcomes, measures and time of measurement during the study.

Secondary outcomes	Measures	Visits		
		Baseline visit, Month 0	Remote, 12‐month follow‐up	Remote, 24‐month follow‐up
Health outcomes	Composite renal end points: End‐stage kidney disease (defined as dialysis, transplantation, or a sustained (>3 months) estimated Glomerular Filtration Rate [eGFR] of <15 mL/min/1.73 m^2^) Doubling of the serum creatinine level Or death from renal causes 3‐Point MACE (non‐fatal myocardial infarction, non‐fatal stroke and cardiovascular death) and components of the extended MACE All‐cause mortality Lower limb major amputation Self reported re‐ulceration		X	X
Patient‐reported outcomes	Using Questionnaires: Distress using Problem Area in Diabetes‐20 (PAID‐20) Self‐efficacy using Diabetes Management Self‐Efficacy Scale‐15 (DMSES‐15) Quality of Life using Diabetes Foot Ulcer Disease (Diabetes Foot Scale‐Short Form [DFS‐SF], generic EuroQoL‐5Dimension‐5Levels [EQ‐5D‐5L]) Depression and anxiety using Hospital Anxiety and Depression Scale (HADS) Health resource use, such as primary care visits, emergency department visits, hospitalisations and medication use using Modular Resource‐Use Measure (ModRUM) Medication adherence using the Morisky Medication Adherence Scale (MMAS‐8) Diet using the Short Form Food Frequency Questionnaire Sleep duration/quality and physical activity volume/intensity measured objectively using wrist worn accelerometers	X	X	X
Biomedical markers	Blood pressure (systolic, diastolic and heart rate) (mmHg, BPM) Low‐density lipoprotein‐cholesterol (LDL‐C) (mmol/L) High‐density lipoprotein‐cholesterol (HDL‐C) (mmol/L) Total cholesterol (TC) (mmol/L) Triglycerides (TG) (mmol/L) Glycated haemoglobin (HbA1c) (% and mmol/mol) Estimated Glomerular Filtration Rate (eGFR) (mL/min/1.73 m2) Urine albumin: creatinine ratio (uACR).	X	X	X
Anthropometric	Weight Body mass index (BMI)	X	X	X
Demographic variables (collected for exploratory stratified analyses)	Age Sex Ethnicity T2DM duration DFUD duration Socio‐economic score (Index of Multiple Deprivation (IMD): a postcode‐based measure of socio‐economic score) Medications (glucose‐lowering, lipid‐lowering, blood pressure‐lowering, antiplatelet and antidepressants)	X	X	X
CGM Metrics	Time in range 3.9‐10 mmol/L Time above range (>10 mmol/L) Time below range (<3.9 mmol/L) sensor usage data (proportion of time the sensor is used)	X	X	X

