#### Questionnaires

2.4.6

Participants will complete the following questionnaires at baseline, 12 and 24 months (Table 1):
EuroQol 5‐Dimension 5‐Level (EQ‐5D‐5L): Measures health‐related quality of life (QoL) specifically in chronic health conditions.Hospital Anxiety and Depression Scale (HADS): Measures the severity of symptoms of anxiety and depression.ModRUM: Includes questions on healthcare resource use covering emergency care, outpatient care, GP visits (including home‐visit or remotely accessed) and NHS HCP visits.Diabetic Foot Ulcer Scale–Short Form (DFS‐SF): Assesses the impact of foot ulcers and their treatment on the QoL of people with diabetes.Diabetes Self Management Efficacy Scale (DMSES‐15): Assesses respondents' confidence levels in their blood sugar, diet and level of exercise management.Problem Areas in Diabetes Questionnaire (PAID‐20): Measures diabetes stress.Morisky Medication Adherence Scale (MMAs‐8): Measures medication‐taking behaviour.Diet (short‐form food frequency questionnaire): Assesses dietary habits.

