#### Blinding

2.4.8

Given the design of the intervention, the study team and participants will not be blinded to the intervention. The study statistician is masked, but no code‐break or emergency unblinding will be required. To reduce bias, the primary and most of the secondary outcomes will be collected from the participants' medical records rather than specifically collected for the study. The patient‐reported secondary outcomes will be collected using validated questionnaires. As such, there are no outcome assessors involved in the study.

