**FIGURE 2 dme70028-fig-0002:**
[figure not shown]
Components of the MiFoot Intervention.

Prior to participation in the physical activity component of the intervention, participants will undergo precautionary screening to ensure safety. This will include an electrocardiogram (ECG) to identify any potential undiagnosed cardiac problems, assessment of any active ulcers and completion of a specifically designed assessment form to safely determine participants' readiness and ability for physical activity.

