### Follow‐up assessments

3.1

Participants will be followed up for 24 months using the same measures as the baseline visit through questionnaires, accelerometers, routine health data and health outcomes (Tables 1 and 2). There will be no on‐site visits for the 12‐ and 24‐month assessments.

**TABLE 2 dme70028-tbl-0002:** Schedule of procedures.

Procedures	Visits			
	Pre‐screening	Baseline visit, Month 0	Remote, 12‐month follow‐up	Remote, 24‐month follow‐up
Invitation and EOI	XX			
Telephone screening	XX			
Informed consent		XX		
Face to face eligibility screening		XX		
Demographics		XX		
Baseline Research Data Extraction		XX		
SINBAD Score		XX		
Consent		XX		
Inform GP of study participation		XX		
Randomisation		XX		
Anthropometric		XX	XX	XX
Patient‐reported outcomes Questionnaires		XX	XX (±4 weeks)	XX (±4 weeks)
Accelerometer		XX (±4 weeks)	XX (±4 weeks)	XX (±4 weeks)
CGM provision		XX^a^		
ECG		X		
Health outcomes data collection		XX	XX	XX
Biomedical markers		XX	XX	XX
Physical activity screening		X		
Adverse event assessments Safety measures		X	X	X
Process evaluation observations		X		
Process evaluation feedback surveys		X^b^		
Process evaluation questionnaires			X	
Process evaluation interviews				After 24th month

*Note*: X: Intervention arm only; XX: All study participants.

Abbreviations: ECG, electrocardiogram; EOI, expression of interest; GP, general practitioner; SINBAD, ulcer site, ischemia, neuropathy, bacterial infection, area and depth.

^a^
All participants will be offered CGM devices at their baseline appointment; though if they decline at this stage, they can change their mind throughout the trial.

^b^
After each one‐to‐one and group sessions and 4 weeks after the digital programme, collected up to month 9 of the intervention delivery.

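### Re-ulceration rests on unblinded, unverified self-report, while extra ulcer assessment, education and adverse event collection occur only in the intervention arm, so differential ascertainment is possible in either direction

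*Protocol article*

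**What the plan says.** Table 1 (Section 2.4.3) places "Self reported re‐ulceration" among the health outcomes, marked at 12 and 24 months but not at baseline. No check of the report against another source is described.

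Section 2.4.8 (Blinding) states that "the study team and participants will not be blinded to the intervention". It then gives two safeguards. First, "the primary and most of the secondary outcomes will be collected from the participants' medical records rather than specifically collected for the study". Second, "The patient‐reported secondary outcomes will be collected using validated questionnaires". From these it concludes that "there are no outcome assessors involved in the study". Section 3.1 adds: "There will be no on‐site visits for the 12‐ and 24‐month assessments".

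Section 2.4.6 lists the questionnaires. The foot-ulcer instrument among them is the DFS-SF, described thus: "Assesses the impact of foot ulcers and their treatment on the QoL of people with diabetes".

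On foot assessment, Section 2.4.2 has SINBAD scored at baseline if an ulcer is active, and Table 2 marks it for all participants. Before the physical activity component, the text after Figure 2 requires "assessment of any active ulcers and completion of a specifically designed assessment form". Table 2 marks physical activity screening, and the adverse event and safety row, with the symbol for the intervention arm only; the latter is so marked at baseline, 12 and 24 months.

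**The concern.** In an open-label trial the credibility of a secondary outcome depends on how it is ascertained. The protocol recognises this and relies on its data sources to stand in for blinding. Re-ulceration falls through that argument. It depends on what an unblinded participant notices, recalls and chooses to report, and the two arms do not reach that point by the same route. Intervention participants may have had an additional ulcer assessment, a 1:1 appointment covering weight-bearing status, and facilitated group education; controls have usual care.

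The outcome bears on safety. The Discussion (Section 8) notes that these patients are commonly advised to restrict weight-bearing for fear of ulceration and amputation, and the Introduction presents the programme's exercise as avoiding further foot problems. A reporting difference could create a false signal of foot harm or conceal a real one. In Table 2 as printed, controls also have no scheduled adverse event assessment against which self-report could be compared.

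**Working it through.** **No plan figure to reproduce.** The document gives no re-ulceration rate, reporting accuracy or power for this outcome. The check is therefore a comparison of the text, followed by an illustration on assumed values.

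**Step 1: is the outcome inside the stated safeguards?**
- Record-based collection: no. Table 1 names self-report as the source, and Section 2.4.8 claims records only for most secondary outcomes.
- Validated questionnaires: not as described. None of the eight instruments in Section 2.4.6 is said to record ulcer occurrence. The DFS-SF measures quality-of-life impact.
- Study examination: none at 12 or 24 months in either arm.

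**Step 2: what differs by arm?**

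| Item | Intervention | Control | Source |
|---|---|---|---|
| SINBAD at baseline, if ulcer active | Yes | Yes | 2.4.2, Table 2 |
| Self-report at 12 and 24 months, remote | Yes | Yes | Table 1, 3.1 |
| Health outcomes data collection at 12 and 24 months | Yes | Yes | Table 2 |
| Ulcer assessment at physical activity screening | Yes | No | Text after Figure 2, Table 2 |
| 1:1 appointment and group education | Yes | No | 2.5.2 |
| Adverse event assessments | Yes | No | Table 2 |

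The collection schedule is the same in both arms. What differs is the contact that may influence what is noticed and reported.

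**Step 3: illustration (assumed values, not from the document).** Let the true 24-month risk be p in both arms, with no false reports. Reported risk = p × reporting sensitivity, so the apparent ratio = sensitivity (intervention) ÷ sensitivity (control), and p cancels.
- 90% vs 80%: 0.90 ÷ 0.80 = 1.125, or about 1.13. At p = 30%: 0.30 × 0.90 = 27% vs 0.30 × 0.80 = 24%.
- 80% vs 90%: 0.80 ÷ 0.90 = 0.89. A true ratio of 1.125 would then appear as 1.125 × 0.889 = 1.00, so the harm would be hidden.
- Equal sensitivity: 1.00.

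**Step 4: chance of a misleading significant result.** Take 372 ÷ 2 = 186 per arm from the sample size section and a two-proportion comparison at two-sided 5%. With 90% vs 80% reporting and no true difference, the chance of a significant result in the direction of the bias is:

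| True risk | Reported risks | Chance |
|---|---|---|
| 20% | 18% vs 16% | 7.4% |
| 30% | 27% vs 24% | 9.7% |
| 40% | 36% vs 32% | 12.6% |
| 50% | 45% vs 40% | 16.2% |

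Without bias the chance in that direction is 2.5%. With 90% vs 70% the ratio is 0.90 ÷ 0.70 = 1.29 and the chance runs from 18% to 50% over the same risks. A larger sample would not remove the bias; it would only estimate the biased ratio more precisely.

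**The case against.** The strongest reply is that nothing here is concealed. Table 1 labels the measure as self-reported, Section 2.4.8 claims records for most secondary outcomes and not all, and the primary outcome and sample size are untouched. The topics listed for the group education do not mention foot inspection, the components are optional (Section 6.2), and the extra ulcer assessment is marked at baseline only. The sensitivities are assumed, and at 90% vs 80% the distortion is modest. All of this stands, and it limits the size and certainty of the point. It does not supply a safeguard for this outcome.

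A second reply also stands in part: moving to records does not remove the problem. If extra contact with healthcare professionals leads to more ulcers being noticed, it may also lead to more being presented and recorded.

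A reader might infer more than the document supports:
- That only the intervention arm has its feet assessed. SINBAD is scored in both arms at baseline when an ulcer is active.
- That controls are questioned on a thinner schedule. Both arms have the same remote 12- and 24-month collection.
- That the arms will report differently, or that the direction is known. The document shows unequal conditions, not unequal reporting.
- That re-ulceration in someone with an unhealed ulcer at entry is left undefined. People with a current ulcer are eligible (Section 2.3.1), but that definition commonly sits in the full protocol, which is not shown.

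**Conclusion.** The point holds as a weakness in the chosen data source. The article fixes re-ulceration as self-report in an open-label trial with no outcome assessor and no on-site follow-up, outside both of its own safeguards, while several sources of extra ulcer attention are intervention-only. Differential ascertainment is possible in either direction, and neither its presence nor its size can be established from the document. The apparent ratios of 1.13 and 0.89 rest on assumed reporting rates of 90% and 80%, equal true risk and no false reports. The effect is confined to one secondary outcome, which matters because it is relevant to foot safety; the primary analysis is unaffected.

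**What to change.** In Table 1, add record-based ascertainment of new foot ulcers after randomisation, done identically in both arms within the health outcomes collection that Table 2 already schedules for all participants at 12 and 24 months. Keep self-report beside it. Report the between-arm comparison from records alongside the one from self-report, show agreement between the two sources by arm, and draw no foot-safety conclusion from self-report alone.

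The cost is a few extra extraction fields. The limits should be stated. Ulcers never presented to care will be missed. Those recorded without a site or healing date may be impossible to classify as new, and the document does not say how completely these details are recorded. Extra professional contact may still raise recording in the intervention arm, so residual detection bias should be acknowledged when results are reported.
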